### Data management {19}

Data collection and entry are combined as electronic data capture is used in the TUMT-PAE-1 trial. Various REDCap tools will be used to ensure the accuracy of data entry and coding. Field Notes will be used to define the metric unit accepted and give short definitions of the requested variable. Field Annotations provide a thorough explanation of each variable and can be used for reference purposes regarding the denotation of the field and how data should be entered and assessed. Field Annotations can be found in the electronic Data Dictionary Codebook made available for study personnel through REDCap. Dropdown lists, radio buttons, and checkboxes will be preferred for data entry to ease data storage, review, and analysis. When text boxes are used, REDCap Validation Rules will be applied, and an error will be displayed if the entry does not meet the criteria of the data type and value. This will promote data quality by narrowing down the input options of text box fields. The Required Field function is used so that data entry cannot be marked as complete before all data is captured; this will ensure collection of all outcome measures. REDCap users will only gain access to the project when assigned by the PI, who will also define the roles of each user with limited privileges. All data will be stored in REDCap for 10 years after the trial ends. No data from this trial will be sent abroad.

### Confidentiality {27}

Before informed consent, the subject’s health records will be screened for inclusion only by the treatment-responsible urologist. Relevant data collected before the informed consent will be shared with the study team. Signing the informed consent gives the study researchers direct access to the subject’s health records to retrieve information necessary to conduct the study. By Danish law, all data will be made available to third parties for control purposes (external monitoring, quality control, etc.). Personal data will be stored electronically in REDCap following the Danish Data Protection Regulation (Databeskyttelseforordningen), the Danish Data Protection Act (Databeskyttelseloven), and the Danish Health Law (Sundhedsloven). Several tools in REDCap will be used to protect confidentiality before, during, and after the trial. In this multicentre study, data access groups (DAGs) will be created in REDCap for restriction of viewing. DAGs will preserve data confidentiality by ensuring that study personnel can only view data from their centre. To protect data and maintain its validity, data access and privileges will be limited by defining user rights and roles in the REDCap database. User rights will be restricted according to the minimum necessary for individuals to complete their assigned tasks. Only the PI will be able to view all records and extract data. Personal data according to the General Data Protection Regulation (GDPR) will be pseudonymised with a serial code ID number. If the patient withdraws consent, no further data will be collected. Data collected up until withdrawal will be stored and used for study purposes. Patients possess the right to be informed about the location of their data storage, the entities utilising it, and the specific purposes for which it is employed. At any given time, they retain the prerogative to request a copy of their study data, either for personal use or for sharing with others. Furthermore, patients are entitled to rectify any inaccuracies present in their personal data. They also have the authority to object to or restrict the utilisation of their data and can demand its deletion as needed.

### Plans for collection, laboratory evaluation, and storage of biological specimens for genetic or molecular analysis in this trial/future use {33}

N/a. No biological material will be stored after analysis.

## Statistical methods

### Statistical methods for primary and secondary outcomes {20a}

The primary endpoint will be evaluated using a 95% confidence interval against the predefined non-inferiority threshold of + 3 points in the IPSS. PAE is expected to be inferior to TUMT by + 1 point on the IPSS within the non-inferior margin allowing the favour of TUMT of + 3 points in the IPSS. To control for initial differences between groups that might affect the result, the primary analysis will be adjusted for site and baseline IPSS. Normal distribution is predicted, and a parametric test will be used. The difference in mean IPSS is expected to be tested with analysis of covariance (ANCOVA) for non-inferiority. Secondary outcomes will be represented descriptively and analysed according to the data type (categorical or continuous) and their distribution. Likely data representations are median with interquartile range and mean with SD for continuous variables and proportions of categorical variables. We plan to compare the secondary outcomes statistically using Student’s *t*-test, chi-square test, and linear mixed models. Statistical analysis will be undertaken using R version 3.2 or later if available. The Eq. 5d package in R will be used to perform the calculation for the economic evaluation of health care from the EQ-5D-5L. In case of deviations from the statistical analysis plan, the information on clinicaltrials.gov will be updated.

### Interim analyses {21b}

The trial will be conducted as a traditional fixed-sample design. An interim analysis of the safety of both procedures will be performed for every 50 cases at 6-month follow-up. The trial-initiating group will have access to the interim results and make the final decision if the trial is to be terminated.

### Methods for additional analyses (e.g. subgroup analyses) {20b}

To address disparities between study groups, we plan to perform additional adjusted analyses correcting for baseline prostate size, age, and Qmax. No additional subgroup analysis is planned at the initiation of this trial.

### Methods in analysis to handle protocol non-adherence and any statistical methods to handle missing data {20c}

The study is analysed as intention-to-treat. As data is expected to be missing completely at random, missing data will be handled by pairwise deletion.

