### Criteria for discontinuing or modifying allocated interventions {11b}

The patient can withdraw the informed consent and leave the study at any time without explanation. If the patient withdraws consent, no further data will be collected. The data already collected until that point will be stored and used for study purposes. If the patient requests to change the treatment option after randomisation, he will be referred to his respective department of urology for his preferred treatment option and included in the analysis as intention-to-treat. The study can be closed prematurely if any untoward patient complication is observed in either treatment arm, defined as serious adverse events (SAEs) resulting in organ failure or death.

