### Relevant concomitant care permitted or prohibited during the trial {11d}

As a pragmatic study, any concomitant care that the treating physician finds relevant is permitted during the trial but will be registered.

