The secondary outcomes include the following:The mean IPSS of the two arms at all other follow-up occasions than the primary outcome.The mean procedure time for the conduction of TUMT and PAE as well as the calculated necrosis.Health-related quality of life measured by the mean IPSS-QoL, BII, and EQ-5D-5L. IPSS-QoL assesses the quality of life associated with symptoms from urinary problems. The BII is a self-reported, validated, disease-specific instrument for quantifying the interference of LUTS on the patient’s mental health and activity. As a measure of QoL, it is used to determine treatment outcomes in men with symptomatic benign prostatic hyperplasia [22]. The EQ-5D is the most widely applied instrument for health-economic assessment worldwide. Its index values are used in the estimation of quality-adjusted life year gains in economic evaluations of healthcare interventions [23].Mean satisfaction with treatment by a five-level bipolar Likert scale.Erectile function measured by the mean IIEF-EF score. The IIEF-EF domain score is a PROM used to measure erectile performance and assess disease severity in efficacy trials. It distinguishes between men with and without erectile dysfunction (ED), classifies levels of ED severity, and has the requisites to detect treatment-related changes in patients with ED [24, 25].Ejaculatory function measured by the mean DAN-PSS-1-sex. The DAN-PSS-1-sex is a validated instrument to determine erectile and ejaculatory function and its impact on the well-being of the patient [26].Incontinence measured by the mean ICIQ-UI-SF. The ICIQ-UI-SF is validated for evaluation of the frequency, severity, and impact on QoL of urinary incontinence [27].Mean prostate volume (PV) measured by TRUS in mL.Mean uroflowmetry outcomes of the two arms. We will be looking at voided volume, Qmax, and residual urine. Uroflowmetry is a non-invasive procedure used to measure the flow of urine throughout micturition. It provides useful information about the total voiding function and is used for diagnosis of lower urinary tract dysfunctions and evaluation of treatment response. Qmax is the value of the highest flow rate measured during the test; it will be set to zero if the patient has an indwelling catheter. Transabdominal ultrasound will be used to assess post-voided residual urine as it is accurate and non-invasive [28].Post-procedure catheterisation events, including the placement of an indwelling urinary catheter and the use of intermittent catheterisation. Catheterisation will be expressed as the reason for placement, duration, and frequency (in case of intermittent catheterisation). If an indwelling catheter is placed after the procedure, the post-procedure duration of catheterisation will be defined as days from the procedure till indwelling catheter cessation. Catheterisation for any other reason during the follow-up period will also be evaluated.Prostate-specific antigen (PSA) and creatinine. The absolute value of serum PSA (ng/mL) has a good predictive value for the determination of prostate volume. Continued PSA measurements assist in the detection of any de novo prostate cancer or progression of patients in active surveillance or watchful waiting. A rise in serum creatinine can be a result of BPH with urinary retention. Serum creatinine aids in the identification of any affection of the kidney from the procedures.De novo use of pharmacological LUTS treatment and surgical re-treatment rates will be collected from the patient’s health record.Incidence at 3 months post-procedure of urinary tract infection, acute urinary retention, dysuria, haematuria, post-embolisation syndrome (PES), hospital admission, and hospitalisation time. PES is defined as occurring within 48 h after surgery and consisting of influenza-like symptoms, pelvic pain, nausea, dysuria, or transient worsening of LUTS. Data on AEs and side effects will be collected from the patient’s health record and the follow-up visit at 3 months. Surgical complications will be categorised following the Clavien-Dindo grading [29].

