**Assessments**								
Likert scale			**X**	**X**				
PROMs (IPSS, IPSS-QoL, BII, EQ-5D-5L, ICIQ-UI-SF, IIEF-EF, DAN-PSS-1-sex)	**X**			**X**	**X**	**X**	**X**	**X**
Catheter use	**X**			**X**	**X**	**X**	**X**	
Technical details of the procedure				**X**				
AEs/SAEs				**X**				
Re-treatment rates						**X**	**X**	**X**

*CTA* computed tomography angiography, *TRUS* transrectal ultrasound, *MRI* magnetic resonance imaging, *PSA* prostate-specific antigen, *PROM* patient-reported outcome measure, *IPSS* International Prostate Symptom Score, *IPSS-QoL* International Prostate Symptom Score—Quality of Life, *BII* Benign Prostatic Hyperplasia Impact Index, *ICIQ-UI-SF* International Consultation on Incontinence Questionnaire—Urinary Incontinence Short Form, *IIEF-EF* International Index of Erectile Function—Erectile Function, *DAN-PSS-1-sex* Danish Prostatic Symptom Score—sexual questions, *AE* adverse event, *SAE* serious adverse event

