## Assignment of interventions: blinding

### Who will be blinded {17a}

N/a. This is an open-label trial; both study personnel and patients will be aware of the received treatment. Due to the physical component of the surgical procedures and outcome assessments, blinding of the patients, surgeons, and outcome assessors has not been possible in our setting. The data analyst will be blinded by having an independent statistician who will be blinded to treatment group allocations conducting the analysis.

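### Intention-to-treat stands alone in an open-label non-inferiority trial that lets men change treatment, so no analysis would show dilution by cross-over

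*Protocol article*

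**What the plan says.** Section 20c, which covers protocol non-adherence and missing data, states: "The study is analysed as intention-to-treat". It names no second analysis set.

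Section 11b allows a man to change treatment after randomisation: "he will be referred to his respective department of urology for his preferred treatment option and included in the analysis as intention-to-treat".

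Section 11d places no limit on other treatment: "any concomitant care that the treating physician finds relevant is permitted during the trial but will be registered". Under Outcomes, "De novo use of pharmacological LUTS treatment and surgical re-treatment rates will be collected" from the health record, as a secondary outcome. Nothing says how such treatment bears on the 6-month IPSS. In Table 1 the row "Re-treatment rates" is first marked at 1 year, after the primary endpoint.

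The trial is open label (section 17a): "both study personnel and patients will be aware of the received treatment". The only additional analyses (section 20b) adjust for baseline prostate size, age and Qmax. They do not change who is analysed or in which arm.

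**The concern.** Non-inferiority is claimed if the upper 95% confidence limit for PAE minus TUMT lies below +3 IPSS points. In a superiority trial, men who cross over work against the claim. Here they work for it: if PAE is worse, a man allocated to PAE who has TUMT improves the PAE mean, and a man allocated to TUMT who has PAE worsens the TUMT mean. Both reduce the observed difference.

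The design makes switching plausible. Allocation is known to everyone, a change is granted on request, and Table 1 puts randomisation in a screening window of day −365 to −2, so a man may know his arm for many months before the procedure. The 10% dropout allowance covers only loss to follow-up for the primary outcome.

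A further LUTS procedure or a new LUTS drug before month 6 (called rescue below; the article does not use the word) could also mask a poorer result, depending on how it falls between the arms. At stake is whether a PAE result at the edge of the margin could be declared non-inferior more often than the nominal 2.5%, without any planned analysis showing why.

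**Working it through.** **Inputs from the article.** Margin +3, one-sided alpha 0.025, SD 5, assumed true difference +1, 100 per arm, 223 after 10% dropout (Sample size). The article gives no cross-over or rescue rate, so every such rate below is an assumption.

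**Formula.** With n per arm and expected observed difference δ, the chance of claiming non-inferiority is

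P = 1 − F(t₀.₉₇₅; 2n − 2, λ), with λ = (3 − δ) / (SD × √(2/n)),

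where F is the noncentral t distribution. For n = 100 and SD 5 the standard error is 5 × √0.02 = 0.707.

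**The plan's own figure.** With δ = 1, λ = 2 / 0.707 = 2.83 and power is 80.4% at 100 per arm (79.97% at 99). So 100 per arm is reproduced, and 200 / 0.9 = 222.2 gives 223. The sample-size arithmetic is not at issue.

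**Cross-over.** If a fraction c of each arm receives the other trial treatment, δ = 3 × (1 − 2c). With PAE truly worse by 3:

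| c, each way | δ | λ (SD 5) | False non-inferiority, SD 5 | SD 6.4 |
|---|---|---|---|---|
| 0 | 3.00 | 0 | 2.5% | 2.5% |
| 2.5% | 2.85 | 0.21 | 4.0% | 3.6% |
| 5% | 2.70 | 0.42 | 6.2% | 5.2% |
| 10% | 2.40 | 0.85 | 13.2% | 9.7% |

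SD 6.4 pools the two 12-week SDs that the article cites: √((6.3² + 6.5²)/2) = 6.40. If men cross in one direction only, δ = 3 × (1 − c), and 5% or 10% gives 4.0% or 6.2% at SD 5.

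**Rescue before month 6.** With rescue rates rP (PAE) and rT (TUMT) and a gain of g points per rescued man, δ = 3 − g × (rP − rT). At SD 5:

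| rP | rT | g | δ | False non-inferiority |
|---|---|---|---|---|
| 10% | 10% | 5 | 3.00 | 2.5% |
| 5% | 10% | 5 | 3.25 | 1.0% |
| 10% | 5% | 5 | 2.75 | 5.4% |
| 8% | 2% | 3 | 2.82 | 4.4% |
| 8% | 2% | 5 | 2.70 | 6.2% |
| 8% | 2% | 10 | 2.40 | 13.2% |

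The direction depends on which arm has more rescue, or gains more from it.

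**Would dropping rescued men help?** Take 8% against 2%, and assume that these men would otherwise score 10 points above the rest. Among the men who remain, the difference is 3 − 10 × (0.08 − 0.02) = 2.4, again below the true 3. In simulation at 100 per arm and SD 5, with a 10-point gain, the false claim rate is about 13% under intention-to-treat, about 13% after exclusion, and about 11% if both must pass. With a 5-point gain, exclusion is worse than intention-to-treat (about 13% against 6%).

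**Cost in power.** With true difference +1 and 90 per arm, power is 76% at SD 5. At SD 6.4 it is 55%, against 59% at 100 per arm.

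**The case against.** The strongest reply is that this is a condensed article, that a separate analysis plan is mentioned and not shown, and that supporting sets are often specified there. Intention-to-treat also suits a trial that calls itself pragmatic and compares the effectiveness of two procedures. The second part stands: intention-to-treat is a sound primary analysis here. The first stands only in part. The article addresses non-adherence in two places and gives intention-to-treat as the whole answer each time. If the unseen plan has a supporting analysis, section 20c should say so.

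Several limits on size also stand. A man's preferred option need not be the other trial arm, since the section on comparators lists other treatments; the formula 3 × (1 − 2c) assumes that it is, equally in both directions. A reader might infer that rescue as well as switching always pulls the arms together. The documents do not support that: equal rescue with equal gain is neutral, and more rescue in the TUMT arm makes the claim harder. Nor is there a basis for crediting each rescued man with 10 points. That figure in the Background is the approximate fall 3 months after TUMT or PAE, not the gain from a second treatment or a new drug.

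A reader might also infer from Table 1 that re-treatment before 1 year goes unrecorded. Sections 11d and 12 already provide for registering concomitant care and for collecting new LUTS drugs and re-treatment from the health record. What is missing is a stated use of those data in relation to the 6-month IPSS.

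**Conclusion.** The point holds for switching: intention-to-treat is the only analysis the article names, in an open-label non-inferiority trial that grants a change of treatment on request, and no supporting analysis would expose dilution. At the margin, with SD 5 and 100 per arm, the false non-inferiority rate would be 4.0%, 6.2% or 13.2% for cross-over of 2.5%, 5% or 10% each way, instead of 2.5%. These figures illustrate sensitivity and do not predict the trial's error rate, since the cross-over rates are assumed. They also apply to a true difference at the margin: if PAE were worse by 4 points, 10% cross-over each way would give about 1.3%.

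Rescue adds to the problem only if it is more frequent or more effective in the PAE arm. That is plausible if PAE is inferior and need follows symptoms, but the documents do not establish it.

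It would be too strong to conclude that intention-to-treat is the wrong primary analysis or that the trial cannot support its claim. This is an inexpensive gap worth closing before outcomes are analysed by arm.

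**What to change.** Keep intention-to-treat as the primary analysis and extend section 20c as follows.

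1. Pre-specify a per-protocol analysis of men who received their allocated procedure, with the same model and the same +3 margin. Require a consistent result before concluding non-inferiority, and define consistent in advance, for example an upper 95% limit below +3 in both analyses. Because this set is selected after randomisation and can itself be biased, it should support intention-to-treat and not replace it.
2. Do not exclude men from that set because of a later LUTS procedure or new LUTS drug. Dropping treatment failures can flatter the worse arm.
3. Handle rescue in a separate pre-specified sensitivity analysis that keeps these men and replaces an IPSS taken after rescue with the last value before it, or another unfavourable value. Check separately the men whose baseline was assigned 35 because of catheter use, since carrying that value forward could dominate the result.
4. Use the data already collected under sections 11d and 12, and report the date of each switch, procedure or new drug relative to the 6-month IPSS, because the Table 1 re-treatment row starts only at 1 year.

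Arms, visits and sample size are unchanged. The cost is a little more analysis and a slightly harder claim. If 90 per arm remain in the supporting set, its power is about 76% on the plan's inputs, against 80% at 100 per arm; at SD 6.4 it is about 55%, against 59%. The rule should be fixed before 6-month outcomes are examined by arm, since a later addition would look data-driven.

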### Outcomes {12}

The outcome measures used in this trial generally follow the registry network for surgical treatment of BPH recently developed [20]. The primary outcome is the mean IPSS of the TUMT and PAE arm 6 months after the procedure. The IPSS is a validated, reproducible, patient-reported outcome measure (PROM) to assess LUTS severity and response to treatment. This measure was selected as the primary outcome as it is the most clinically relevant and internationally accepted PROM for assessing LUTS [21].

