### Sample size {14}

A non-inferiority study design was chosen based on several case studies on the efficacy of TUMT and PAE in men with similar inclusion criteria as this trial. From a review of TUMT, a study with a baseline IPSS above 19 and follow-up after 3 months was selected [30]. In this study, the IPSS 12 weeks after TUMT had decreased to 11.3 with a standard deviation (SD) of 6.3 [8]. With PAE, a recent independent study has demonstrated an IPSS at baseline of 19.4 with an SD of 6.3. Twelve weeks after the procedure, the IPSS declined to 10 with an SD of 6.5 [7]. The difference of approximately 1 IPSS point between the two treatments holds for 6- and 12-month follow-up according to the data available in systematic reviews [10, 12, 31]. Due to resource constraints of our trial and the great variation in SD across TUMT and PAE trials, we have chosen an SD of 5 [30, 32]. The sample size calculation was based on “Sample sizes for clinical trials with normal data. *Statist. Med.* 2004; 23:1921–1986” by Julious [33]. The size was calculated using the package “PowerTOST” in R for the sampleN.noninf() function in R set to parallel design. We used a one-sided significance level of 0.025. Power was set at 80%. Assuming a difference in mean IPSS after treatment of + 1 point in the favour of TUMT with an SD of 5 and a non-inferiority margin set at the border for a clinically non-meaningful difference of + 3 points in the favour of TUMT [34, 35], the calculated size was 100 per group, giving a total size of 200 patients. Dropouts are defined as patients who after inclusion are lost to follow-up for the primary outcome. To compensate for an anticipated dropout rate of 10%, the study will include 223 patients.

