### Concealment mechanism {16b}

REDCap allocates the patient when baseline measures have been completed and the informed consent signed, in that way the allocation concealment will be guaranteed.

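### The unsupported MCAR assumption and deletion rule drop men without a 6-month IPSS from the only confirmatory test; the resulting bias can go either way

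*Protocol article*

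**What the plan says.** Section {20c} of the protocol article has two sentences on this. The first sets the population: "The study is analysed as intention-to-treat". The second sets the handling of missing data: "As data is expected to be missing completely at random, missing data will be handled by pairwise deletion".

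Other sections show what this means for the primary test:

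- Outcomes {12}: "The primary outcome is the mean IPSS of the TUMT and PAE arm 6 months after the procedure".
- Statistical methods {20a}: the planned test is an ANCOVA, and "the primary analysis will be adjusted for site and baseline IPSS".
- Sample size {14}: a dropout is a man lost to follow-up for the primary outcome. "To compensate for an anticipated dropout rate of 10%, the study will include 223 patients".
- Concealment mechanism {16b}: "REDCap allocates the patient when baseline measures have been completed and the informed consent signed". Table 1 lists randomisation among the screening activities, which run from day −365 to day −2, and times every follow-up visit from the procedure.
- Section {11b}: no data are collected once consent is withdrawn. Men who ask for the other treatment stay in the intention-to-treat analysis.
- Section {18b}: staff pursue men who have not returned questionnaires, with the stated purpose of completing the primary outcome.

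**The concern.** With one outcome value per man in an ANCOVA, pairwise deletion is an available-case analysis: a man without a 6-month IPSS does not count. That is harmless if missingness is unrelated to outcome once arm, site and baseline IPSS are accounted for. The article asserts the stronger condition, MCAR, and gives no reason for it.

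The design makes the assumption doubtful. Patients know their treatment and report the outcome themselves, and collection stops at withdrawal, so men with disappointing results may be less likely to have a score. The IPSS value of 35 for catheterised men is given for baseline only, so some of the worst 6-month results may have no defined score. Because follow-up is timed from the procedure, a randomised man who never has one has no evident 6-month date either.

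Non-inferiority is judged by the upper confidence limit of the PAE minus TUMT difference against +3. If missing failures lie mainly in the PAE arm, the observed difference is too small and the risk of a false claim rises. If they lie mainly in the TUMT arm, the trial loses power.

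**Working it through.** **Inputs from the article.** Margin +3, expected true difference +1, SD 5, 100 analysed per arm, 223 randomised (about 111.5 per arm), 10% missing. On the level: "We used a one-sided significance level of 0.025". The sample size section cites a 12-week IPSS of 11.3 (SD 6.3) for TUMT and 10 (SD 6.5) for PAE. I take SD 6.4 as the midpoint of those two SDs.

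**Assumed, because the article gives only 10% overall.** The missing fraction in each arm (d) and the amount by which missing men's mean IPSS exceeds that of observed men (e).

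**The plan's own figure.** The noncentral t gives power 0.7997 at 99 per arm and 0.8036 at 100, so 100 per arm reproduces. 200/0.9 = 222.2, rounded up to 223, also reproduces.

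**Formulas.**
- Bias toward non-inferiority: b = d(PAE) × e(PAE) − d(TUMT) × e(TUMT).
- SE = SD × √(1/n(TUMT) + 1/n(PAE)). At 100 per arm this is 5 × √0.02 = 0.707 for SD 5 and 6.4 × √0.02 = 0.905 for SD 6.4.
- False-claim rate at a true difference of 3: Φ(b/SE − 1.96).
- Power at a true difference of 1: Φ((2 + b)/SE − 1.96).

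At SE 0.707, non-inferiority is claimed when the observed difference is below 3 − 1.96 × 0.707 = 1.61.

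**Scenario 1: equal failure-related missingness.** 10% in each arm with the same e gives b = 0 and an error of 2.5%. Simulation (20,000 runs, e = 10) gave 2.4%.

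**Scenario 2: 12% PAE, 8% TUMT, e = 9 in both.** b = (0.12 − 0.08) × 9 = 0.36.
- SD 5: Φ(0.36/0.706 − 1.96) = 7.4%.
- SD 6.4: 5.9%.

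**Scenario 3: 10% missing per arm, only the missing PAE men are failures.** Take the TUMT mean at the cited 11.3, a true difference of 3 and missing PAE men at IPSS 20.
- Full PAE mean: 11.3 + 3 = 14.3.
- PAE completers: (14.3 − 0.10 × 20)/0.90 = 13.67.
- b = 14.3 − 13.67 = 0.63.
- SD 5: Φ(0.63/0.707 − 1.96) = about 14%.
- SD 6.4: Φ(0.63/0.905 − 1.96) = about 10%.

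**Scenario 4: the imbalance reversed (SD 5).**
- 12% TUMT, 8% PAE, e = 9: b = −0.36, error 0.7%, and power at a true difference of 1 falls from 0.81 to 0.64.
- 15% TUMT, 5% PAE, e = 10: b = −1.0, error 0.04%, power 0.29.

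In the simulations that were run (equal, PAE-excess and TUMT-excess missingness), analysing every randomised man kept the error at 2.4% to 2.6%.

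**The case against.** The strongest reply is that nothing in the article shows treatment failures being removed. Switchers stay in, concomitant care is permitted and registered, and staff chase the 6-month questionnaire, so a failed patient who returns an IPSS is counted. Adjusting for baseline IPSS and site also means the ANCOVA tolerates missingness that those covariates explain and does not need strict MCAR. All of this stands. It limits the size of the problem but does not justify the assumption for the 10% still expected to lack a score.

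Several stronger readings are tempting, and the documents do not support them:

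- **That the bias must favour PAE.** This needs missing failures to be concentrated in the PAE arm. The side-effect ranges in the harms section do not settle it: the upper limits for urinary tract infection and erectile dysfunction are higher for TUMT, while post-embolisation syndrome is listed only for PAE.
- **That the false-claim rate is about 24%.** This follows from PAE completers at 11, missing PAE men at 20 and a true difference of 3. The full PAE mean is then 11.9 and the TUMT mean 8.9, against the 11.3 the article cites. Scenario 3 holds 11.3 instead.
- **That deletion contradicts intention-to-treat.** Analysing available cases by allocated arm is incomplete intention-to-treat, not a contradiction. The loss of men with no procedure is an inference from the visit timing.
- **That the 3-month IPSS goes unused.** It is a secondary outcome, and mixed models are planned for secondary outcomes. It is only not stated to inform the primary ANCOVA.
- **That sensitivity analyses are missing.** They may be in the statistical analysis plan, which is not at hand.

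**Conclusion.** The point holds as a criticism of a stated rule. The article fixes MCAR and deletion for the primary outcome without support, in a setting where missingness may depend on outcome, and so decides who counts in the sole confirmatory test.

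Across the scenarios the one-sided error runs from 2.5% (balanced) through about 7% to about 14% at SD 5, or about 10% at SD 6.4 in that last case. Below 2.5%, the reversed imbalance costs power instead. These figures rest on assumed arm-specific missingness and score gaps. They show what the rule permits within the planned 10% dropout and do not forecast what will happen.

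**What to change.** Replace the MCAR and deletion rule for the primary outcome:

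1. Use an analysis valid under missing at random over all randomised men: a mixed model for repeated measures, or multiple imputation by arm. Draw on baseline IPSS, 3-month IPSS, site, catheter status and re-treatment. The last two arise after randomisation, so they belong in the imputation model and not as covariates in the treatment comparison.
2. For men who have no procedure, time the 6-month assessment from a defined date, such as the scheduled procedure date, so that they stay in the intention-to-treat analysis. The 3-month IPSS alone will not retain them, because it is also timed from the procedure.
3. Report a delta-adjusted tipping-point analysis: worsen the imputed PAE scores step by step and state where the upper limit crosses +3. If the statistical analysis plan already contains this, refer to it in section {20c}.

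The cost is modest analysis work and possibly a slightly wider confidence interval. The 3-month IPSS is already scheduled, and the sample size stays at 223.
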